#### Cotton-dust exposures

We will use IOM sampling heads with Casella Apex2 pumps for personal monitoring of dust exposures, measuring the inhalable fraction of particulate matter (PM < 100 μm) over an 8-h shift. Pre- and post-sampling airflow and sampling time will be recorded, as well as temperature and humidity readings. Each individual’s average PM exposure concentration will be calculated from the difference in filter weights and sampled air volume. Individual data will then be combined to derive mean exposures for combinations of job and section at each mill. Where possible, the same workers will be monitored at follow-up as at baseline, but those who cannot be re-contacted will be replaced by others with similar job tasks. Dust sampling will be done at all the textile mills across the intervention and control arms at baseline and will be repeated at 3, 12 and 18 months after intervention. In addition to personal sampling, area sampling will be carried out in the spinning and weaving sections of each mill using a Dylos DC 1700 particle counter to measure the average concentration of dust (particle size > 0.5 or > 0.25 μm) over an 8-h shift. The particle counters will be placed at fixed sites in the centres of work stations in the spinning and weaving sections, at approximately 1.5 m height, and away from the ventilation outlets or fans. Side-by-side gravimetric and Dylos measurements will be made for a small number of sites to provide a calibration factor for the Dylos particle concentration in relation to cotton dust.

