### Study outcomes

The primary outcomes of the trial at 18 months post intervention, will be: (1) personal dust exposure levels (in mg/m^3^), and their change from baseline, in the intervention as compared with the control arm; (2) dust levels in different sections of the mill (in mg/m^3^), and their changes from baseline, in the intervention as compared with the control arm; (3) changes from baseline in the prevalence of respiratory symptoms, in the intervention as compared with the control arm (a composite variable will be used for presence of one or more respiratory symptoms including; cough, sputum, wheeze, shortness of breath and chest tightness) and (4) changes in FEV_1_ from baseline to follow-up, in the intervention as compared with the control arm.

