### Statistical power

Based on previous occupational trials, we assumed that the intra-class correlation coefficients for the outcome measures were 0.02 [29, 30].

For cotton-dust levels: assuming the level of significance at 5%, power 80% and a 15% or 0.65 mg/m^3^ difference in mean PM levels in the intervention arm compared to the control arm (expected mean dust level in control arm: 0.6 with a standard deviation of 2.5); the sample size required without clustering is 233/arm. The variance inflation factor is:
$$ \left[1+\left(50-1\right)\ast 0.02\right)\Big]=1.98, $$

so the sample size is inflated to 461, which rounds up to 10 groups of 50 in each arm – which increases to 10 groups of 61 in each arm after inflating for losses (* 1.05 * 1.05 * 1.1 = * 1.212).

For respiratory symptoms: the trial is powered to detect a difference of 10% in the proportion of workers reporting respiratory symptoms between the intervention and control arms. Assuming a level of significance at 5%, power 80%, the proportion of workers having respiratory symptoms at the baseline as 40%; without clustering we would require 354/arm. With clustering, the new sample size is 701/arm which – in groups of 50 – means 14 groups of 50 in each arm of the study. Inflating these numbers for losses gives 14 groups of 61.

For lung function: assuming level of significance at 5%, power 80%, 5% or a 150-ml difference in mean FEV_1_ (standard deviation 31) in the intervention arm compared to the control arm (expected mean FEV_1_ in control arm: 3279 ml, standard deviation 690); the requirement without clustering would be 333 per arm, which inflates to 660 with clustering, which again leads to 14 groups of 50 in each arm and this again inflates to 14 groups of 61 after inflating for losses.

Based on the above calculation, we intend to recruit 854 workers from 14 clusters in each arm, a total of 1708 participants in 28 clusters.

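### The cotton-dust sample size (461 per arm, 80% power) counts workers, so it does not apply to primary outcome 2, section dust, whose power depends on inputs the protocol does not give

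*Protocol article*

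**What the plan says.** All references are to the protocol article.

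- **Study outcomes** lists four primary outcomes at 18 months. The first is personal dust exposure. The second is "dust levels in different sections of the mill", in mg/m3, as levels and as changes from baseline.
- **Statistical power** has one dust calculation, "assuming the level of significance at 5%, power 80% and a 15% or 0.65 mg/m^3^ difference in mean PM levels", with "expected mean dust level in control arm: 0.6 with a standard deviation of 2.5". From this, "the sample size required without clustering is 233/arm". On clustering, "we assumed that the intra-class correlation coefficients for the outcome measures were 0.02". With a variance inflation factor of 1.98, "so the sample size is inflated to 461, which rounds up to 10 groups of 50 in each arm". An allowance for losses then takes every group to 61 workers. The section ends with 854 workers in 14 mills per arm.
- **Cotton-dust exposures** says "area sampling will be carried out in the spinning and weaving sections of each mill using a Dylos DC 1700 particle counter", averaged over an 8-hour shift at fixed positions. The number of positions is not given. The same section also combines personal samples into means by job and section.
- **Recruitment and randomization** limits personal sampling to five workers per mill and admits mills that have only a spinning or only a weaving section.
- **Statistical analysis** plans GEE models that compare changes from baseline and allow for clustering by mill and for repeated measures.

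**The concern.** The calculation is labelled as covering cotton-dust levels in general, and two of the four primary outcomes are dust outcomes. A reader would take both as powered at 80%. The calculation needs about 50 dust values per mill, one per worker. Section dust is not collected that way: its sample size is the number of counter positions per mill times 14 mills per arm, and enrolling more workers does not change it.

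Lowering dust in the spinning and weaving sections is a stated aim of the trial (Background). If a null result on outcome 2 is read against a declared 80% power, it may be taken as evidence that the package does not reduce workplace dust, when the design may have had much less chance of showing the stated difference.

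**Working it through.** **1. The plan's own figure.** Inputs from Statistical power: difference 0.65, SD 2.5, 5% significance (two-sided reproduces the result), 80% power.

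n per arm = 2 × (1.96 + 0.8416)² × 2.5² / 0.65² = 232.2, rounded up to 233. This agrees.

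Inflation factor = 1 + (50 − 1) × 0.02 = 1.98, and 233 × 1.98 = 461.3. That is 461.3 / 50 = 9.2 groups, rounded up to 10. Losses: 50 × 1.05 × 1.05 × 1.1 = 60.6, or 61. The arithmetic is sound, but it assumes about 50 dust values per mill.

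**2. What outcome 2 supplies.** There are 28 mills, 14 per arm. Let s be the area sites per mill. The protocol gives no value for s, so s is an assumption here. It gives no area SD either. I borrow SD 2.5 and ICC 0.02, which is a second assumption.

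SD of a mill mean = 2.5 × √[(1 + (s − 1) × 0.02) / s]. Standard error of the difference = that SD × √(2/14). Power is from the noncentral t with 26 degrees of freedom, for a difference of 0.65.

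| Sites per mill | SD of mill mean | Unadjusted power |
|---|---|---|
| 1 | 2.50 | 10% |
| 2 | 1.79 | 15% |
| 4 | 1.29 | 25% |
| 10 | 0.86 | 49% |

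Reaching 80% takes about 25 sites per mill by the normal approximation and about 28 by the t distribution. With one site, the difference detectable at 80% power is 2.75 mg/m3.

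**3. Allowing for baseline.** If baseline and follow-up mill means correlate at r, adjustment multiplies the SD by √(1 − r²).

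| r | 1 site | 4 sites |
|---|---|---|
| 0.5 | 12% | 32% |
| 0.8 | 20% | 57% |
| 0.9 | 33% | 84% |

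**4. Other assumed values, unadjusted.** An area SD of 1.5 gives 20% to 57% for one to four sites, the same as r = 0.8, because 2.5 × √(1 − 0.64) = 1.5. A mill-mean SD of 1.0 gives 38%. At ICC 0.1 even 30 sites per mill give only 45%.

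**5. The other route to section dust.** If section levels are built from personal samples, there are 5 × 14 = 70 per arm against 461 required. Step 2 with s = 5 gives about 30%.

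**6. The stated difference.** 15% of 0.6 is 0.09, not 0.65; 0.65 is 15% of about 4.33. At SD 2.5 a difference of 0.09 would need 12,113 per arm before clustering. All the power figures above use 0.65 as stated.

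**The case against.** The tempting stronger reading is that power for outcome 2 is 10–25% on the plan's own inputs. The documents do not support that as a fact, for four reasons.

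- **Site count.** The range matches only one to four sites per mill. No number is stated, and at ten sites the figure is 49%.
- **SD.** The calculation speaks of PM levels, and the protocol uses PM for personal sampling. The SD of 2.5 is therefore most naturally a between-worker figure and may not describe 8-hour averages at fixed positions.
- **Analysis.** The plan compares changes from baseline in a repeated-measures model. Readings at the same positions may correlate well over time, and at 0.9 with four sites power passes 80%.
- **Instrument.** Study outcomes does not say outright that outcome 2 is the counter reading, and personal samples are also combined by section.

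The first three points stand, so any power figure has to be given as conditional. The fourth stands as a matter of wording but does not restore the power, because the personal-sample route has 70 values per arm.

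It can also be said that the five-against-50 mismatch for personal dust is the better documented fault, since its sample count is stated. That is true, but correcting it would not settle outcome 2 where the counters supply it, because the instrument, sampling unit and variance differ. Lastly, a condensed article may leave site counts and an area SD to the full protocol. That excuses their absence. It does not excuse a published power statement for cotton dust whose unit one of the two dust outcomes lacks.

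**Conclusion.** Wrong as written. The 461 per arm and its 80% power count workers and do not apply to primary outcome 2; the article gives no other basis for that outcome. This part needs no assumption beyond reading section dust as either the counter readings or section means of personal samples, and it holds under both.

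The size of the shortfall is conditional on sites per mill, area SD, ICC, baseline correlation and the unreconciled 0.65. Power well below 80% is likely across most of the values tried, but it is not proven: a high baseline correlation with several sites, or a much smaller area SD, would change the picture.

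A reader might also infer that outcome 2 should be demoted. That does not follow. Whether to keep a registered primary outcome with limited precision is a trade-off for the sponsor, and the fault lies in the stated power, not in the choice of outcome.

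**What to change.** In Statistical power:

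1. State that the 461-per-arm calculation does not cover section dust.
2. Reconcile the difference given as both 15% and 0.65 mg/m3 with the control mean of 0.6, since every dust power figure depends on it.
3. Say how outcome 2 is obtained (counters or grouped personal samples) and give the planned number of sites per mill.
4. Report the detectable difference for 14 versus 14 mills from the mill-mean SD in the baseline survey, which precedes randomization, with an allowance for baseline adjustment and the assumed correlation stated.

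Outcome 2 may remain primary with that precision stated beside it. The cost is wording and one calculation from data the trial already plans to collect, with no extra recruitment. The downside is a less favourable published figure for one primary outcome.

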### Ethical considerations

The study has received full ethical approval from the Ethics Review Committee at Aga Khan University, Pakistan (2019-0962-3710) and the Research Ethics Committee at Imperial College London, UK (19IC4968), as well as the Research Ethics Committee of the National Bioethics Committee in Pakistan (4-87/NBC-402/19/483). Written informed consent will be obtained from each participant, and they will be free to leave the study whenever they desire. The workers’ workshops will be brief and conducted in small groups so that mill productivity is not affected. A small financial compensation will be provided to each participant at each time of data collection. Workers will be provided with light refreshments after spirometry and during workshops.

All the participants will be informed verbally about their spirometry results and guided accordingly. If a study participant wishes to receive the spirometry report this will be provided. Workers who are found to have significant, previously unrecognized lung disease will be counseled, and if they wish, they will be referred to a suitable government hospital for further evaluation and management. A letter of referral will be provided.

All data will be kept confidential and the questionnaire reports and spirometry results of individual workers will not be shared with their employers. However, employers will be provided with anonymized summary results for their mills at the end of the study to help them plan appropriate control and preventive measures.

The study should help the textile workers to improve their knowledge about the health hazards of cotton-dust exposure and guide researchers further towards developing strategies for the implementation of protective measures. In addition, the textile workers will be tested for their respiratory function through spirometry, which will be free of cost. Those in the intervention arm will also be provided with free disposable face-masks on a daily basis during the study period.

Incentives for the workplaces will include free monitoring of dust levels, employee health assessments and training. Such measures will benefit their audit and compliance processes, and in this way they may be able to get better business by fulfilling the requirements of major textile buyers globally [31]. After the conclusion of this study, by agreement before the trial, expert advice on OHS improvements will also be provided to the mills in the control arm.

### Dissemination

In Pakistan, dissemination seminars will be organized to share findings with various stakeholders including representatives from textile mill associations, concerned non-governmental organizations (NGOs), national and provincial Environmental Protection Agencies (EPAs), Labor Department, Ministry of Textile and Ministry of Health. Textile mill and business associations are key stakeholders for this project. They will help in getting access to the industry and will also facilitate the implementation of policy recommendations that emerge from the research.

## Discussion

This trial will test whether a simple, low-cost intervention package can reduce dust levels in textile mills, and improve the respiratory health of textile workers in developing countries such as Pakistan. The randomized controlled design of the project should provide robust scientific evidence regarding the effectiveness of such an intervention and, if it is found to be successful, will have significant implications for similar settings in Pakistan and elsewhere.

We chose a cluster randomized design since the intervention will have some impact at the individual level, but more so at the cluster level, through changes in the management and the overall organizational plans and practices. Because much of the effect may be at the level of the plant, it would not be possible to randomize individuals.

We will measure the inhalable fraction (≤ 100 μm) of dust at the textile mills in accordance with the Health and Safety Executive (HSE), UK guidelines [32]. The smaller dust particles (≤ 2.5 μm; respirable fraction) are known to be more hazardous compared to the larger ones; however, previous studies demonstrated the feasibility of using the inhalable fraction for assessing cotton-dust exposure among textile workers [33]. Moreover, measurement of the inhalable fraction will allow comparison with cotton-dust standards. Due to logistic and financial constraints, measurement of bacterial endotoxin levels will not be possible in this trial, but we believe that cotton-dust measurements will provide a reasonable approximation of the endotoxin levels and related health effects in Pakistani textile mills [33, 34].

Recruitment of the required number of mills and workers will be challenging. The study team is already in contact with stakeholders in the textile industry in Pakistan and is disseminating wider publicity of the study in Karachi and networking with relevant business associations for better access to textile mills. In order to access textile workers for data collection and training, incentives will be provided for workers, including free spirometry and a small financial compensation for their time.

Several limitations may need to be considered when interpreting the findings.“Contamination” of the control sites might occur if contact with participants or mill representatives from the intervention arm led to the adoption of some of the intervention by mills or workers in the control arm. However, any such contamination should be limited since there are limited opportunities for textile workers in Pakistan to unionize or socialize as a group. Moreover, we will ask the mill management to keep their participation status confidential from other mills until the study has been completed.

Even in the absence of contamination, however, study participants and mill representatives in the control arm of the study may alter their behaviour or introduce OHS initiatives, simply because they know that they are being observed (a Hawthorne Effect). This would tend to dilute the estimated effectiveness of the intervention. We will try to reduce any such bias by providing minimal information on the intervention to the control group. In addition, any changes over the course of the study in the OHS provisions at control mills will be documented, and taken into account in interpretation.

Loss to follow-up may be another problem. Labor turnover is generally high in Pakistani textile mills and workers may also change sections within the same mill. If the worker has switched job to another section within the same mill we will try to approach him for follow-up but if he has moved to another mill, we may not be able to follow him. Where a worker is not able to continue working due to sickness, we will note the information. Loss to follow-up may also occur due to death or outmigration (to another city), although this is less likely. Such losses are inevitable but have been taken into account in setting the sample size.

Despite these challenges, we believe that the study had the potential to generate useful information that may lead to cost-effective policies for the prevention of work-related respiratory disease among textile workers in developing countries.

### Trial status

Recruiting

## Data Availability

Not applicable

## Abbreviations

EOH: Environmental and Occupational Health
EPA: Environmental Protection Agency
FEV_1_: Forced expiratory volume in first second
FVC: Forced vital capacity
GDP: Gross Domestic Product
GEE: Generalized estimating equations
HSE: Health and Safety Executive, UK
IOM: Institute of Occupational Medicine
KAP: Knowledge, attitude and practices
MRC: Medical Research Council, UK
NIHBCC: National Institutes of Health Behaviour Change Consortium
OHS: Occupational health and safety
PM: Particulate matter
PPE: Personal protective equipment
WEL: Workplace exposure limits
